## Ethics and dissemination

### Data management

The research team will preserve the confidentiality of participants in accordance with the 1998 Data Protection Act and 2018 General Data Protection Regulation. Data will be stored on secure information technology systems, which are backed up daily, and data access will be restricted to the trial research team. Paper documentation containing personal data will be stored in locked filing cabinets with restricted access and separate from any research data. Additionally, paper documentation will be scanned and stored in a digitised format in a restricted access drive separate from any research data. Research data and consent forms will be kept for a minimum of 10 years or for as long the research data are archived, in line with the University of Glasgow policy. Audio recordings will be transcribed in full by University of Glasgow-approved contractors with secure and confidential data transfer. Transcripts will be anonymised and stored in secure files, accessible only to named members of the research team, in a separate drive from any personal participant data. Personal contact data will be kept until the completion of the study.

### Project oversight

An independent and funder-approved TSC and DMEC will meet at least annually. The TSC will monitor trial progress, adherence to protocol, participant safety and ethical conduct. The DMEC will monitor data quality and completeness, recruitment and loss to follow-up, and advise on data analysis plans. Both the TSC and DMEC will advise on study conduct and protocol modifications. Approval for protocol amendments will be sought from the chairs of both committees. Membership will include experts in school-based interventions and trials, GBV, as well as an education professional.

### Public and patient involvement

We will establish a Young People’s Advisory Group comprising current and recent senior secondary school students with an interest in addressing school-based GBV. The group will meet online and in person to advise on study materials, processes, outputs and dissemination plans. Members will be recruited via schools undertaking ESAS and existing RCS networks. This group will meet approximately three times a year.

We will also establish an adult public involvement group, comprising school staff and parents/carers (from non-evaluation schools) to advise on study materials, outputs and dissemination plans. This group will meet online approximately two times a year.

### Ethical issues

The study has been approved by the University of Glasgow College of Medical, Veterinary and Life Sciences Ethics Committee (06/06/2023 ref 200220268).

The school leadership team consents to participate in the trial on behalf of the school, including consent to be randomised. Parents/carers will be given opportunity to opt out their child from evaluation activities, after reading an information leaflet. In all data collection activities, it will be made clear to participants that they can decline to participate, or skip specific questions, or withdraw at any time, with no negative repercussions. Informed consent for observation of intervention activities is not practical, but the presence of the observer will be explained where possible, and reassurance given regarding the anonymity of data generated by observations. In group discussions, participants will be reminded that confidentiality cannot be guaranteed and they will be asked to refrain from sharing personal stories or recounting events in a way that makes others identifiable.

### Child protection/safeguarding in the ESAS intervention and evaluation

Discussion of GBV may trigger difficult feelings for participants. To safeguard participant well-being, we will clearly indicate the topics that will be covered; provide lists of support services before and after data collection activities; offer to stop or pause if a participant becomes upset; and interact with students empathically and without expressing judgement. During qualitative data collection, if disclosures are made which suggest an immediate and serious risk of harm to a student or staff member, the researcher will notify the child protection lead for the school (via the study PI), seeking agreement from the participant as far as possible. Such disclosures will be handled confidentially via usual school safeguarding procedures. The baseline and follow-up surveys are anonymous but at the end, students will be able to leave their name via a separate secure online form if they wish a staff member to follow-up with them. The research team will securely pass these names to school staff after each survey and then delete them from their database. In this instance, safeguarding procedures apply, regardless of where the harm took place.

Serious adverse events (SAE) in this study could include incidents of sexual harassment and violence, and mental/physical ill health resulting from such incidents. Incidents of sexual harassment occur in schools regardless of ESAS and are unlikely to result from it. However, disclosures of already-occurring GBV may increase due to greater awareness and confidence to report (an aim of ESAS). We do not plan to specifically track SAEs in the trial because (a) these overlap with primary outcome data already collected by the trial; (b) reported incidents of sexual harassment are highly sensitive and confidential and schools may be unwilling to disclose and/or may view the request for information as burdensome; (c) it is unlikely that any SAE could ever be linked to the trial. We will use the health resource use questions in the student baseline survey to track the likely prevalence of SAEs and we may pick up additional information during check-in meetings between the evaluation team and ESAS staff leads.

Where SAEs become known to the study team (either directly or indirectly), these will be reported internally and to the TSC chair (and sponsor, University of Glasgow, as appropriate) within 24 hours of the study team becoming aware of an event. The University of Glasgow Clinical Trials Unit has standard operating procedures for managing and reporting any SAEs, following guidelines for Good Clinical Practice.

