### Recruitment and randomisation

We will recruit 36 schools across Scotland via a range of methods:

Email invitation to schools who have registered for an ESAS account but not yet logged any ESAS activities (ie, expressed a previous interest in ESAS).Regular advertisements via the Scottish Schools Health Research Network (SHINE) and presentations at their annual conference.Working with local authority education leads to advertise the opportunity to schools in their authority. Local authority education leads will be identified via the SHINE network, existing contacts of RCS and the research team, or via school leads.

Recruitment materials will include a brief for schools outlining the key study stages, including randomisation. School leads expressing interest in the evaluation study will meet with the principal investigator (PI) in person or via Microsoft Teams. They will be advised that participation in the evaluation involves randomisation to immediate or delayed start. Schools who are keen to do ESAS but do not wish to be randomised will be advised that they can implement ESAS outside of the evaluation and in their own timing. We will maintain a log of recruitment meetings and record reasons for non-participation. We will incentivise recruitment and retention by offering a £500 payment to all participating schools with an additional £1000 for case study schools, reflecting the greater research load on these schools. To promote retention, schools will be asked to sign an informal collaboration agreement outlining the roles and responsibilities of RCS, the research team and the school.

Formal recruitment is indicated by completion of the student baseline survey (October 2023 to December 2024). At this point, schools will be randomised (1:1) using minimisation to ensure balance between arms in:

Proportion of students receiving FSM.School roll (size).Whether they are currently undertaking MVP.

Schools will be randomised either to start the ESAS intervention immediately or to continue usual practice and start ESAS after 12 months (delayed start; control condition). The randomisation will be performed using centralised computer-generated randomisation sequence (Sealed Envelope) by trial statistician (AP).

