### Measures

Outcome measures (baseline, 12 months and 24 months).

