#### Secondary outcomes

*Students’ experience of forced sexual activity* will be measured via single item: forced you to do something sexual (at school or the way to/from school in the last 2 months).^40^

*Students’ sexual harassment perpetration* will be measured using three items that assess engagement in unwelcome behaviours at or on the way to or from school in the last 2 months. The 4-month prevalence of perpetrating sexual harassment reported in De Gue *et al*^40^ was 29% (Cronbach’s α=0.73–0.83 across waves); the 3-month estimate from our pilot data was 27% (Cronbach’s α=0.62) (adapted from DeGue *et al*^40^).

*Students’ attitudes towards teen dating violence* will be measured using two items (adapted from Meiksin *et al*^43^).

*Students’ quality of life* will be measured using the Child Health Utility 9D (CHU-9D).^44^

*Students’ mental well-being* will be measured using the 7-item Warwick-Edinburgh Mental Wellbeing Scale (WEMWBS).^45^

*Students’ use of health and social services*. Questions on external health appointments and in-school health professional support (number of appointments of each service type in the last 3 months).

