#### Study 3: economic evaluation

The data for the economic evaluation will be collected via the student baseline and follow-up surveys. Measures include the CHU-9D instrument and a bespoke health economics questionnaire capturing a broad set of resource use (use of health and social services such as general practitioner (GP), school nurse, school counsellor). The cost of the ESAS intervention (actual cost; opportunity cost) and the comparator (ie, standard GBV activities part of school curriculum) will be collected via several sources, including school interviews, ESAS web-based dashboard, qualitative interviews and RCS.

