The baseline and all follow-up surveys will include the preference-based quality of life instrument, the CHU-9D. They will also include a bespoke resource use questionnaire designed to measure cross-sectoral health and social care use (eg, GP and educational psychologist), community services (eg, judicial contacts) and personal health-related activities and costs (eg, private counsellors). Resources required to deliver ESAS (including displaced school activities and their associated opportunity cost) will be measured via resource use logs completed by researchers and informed by school leads. All resources measured will be valued using readily available unit costs.^61^

In line with the SAP, we will follow the approach described by Hooper *et al*,^62^ adapted to account for non-normality of health economic outcomes and costs.

We will estimate the incremental difference in total cost and outcomes using a mixed-effects generalised linear model, adjusted for school-level baseline characteristics such as school size, percentage FSM and MVP status (ie, school partaking in MVP activities). Total cost and outcomes will also be adjusted by baseline costs and outcomes to adjust for any imbalance between treatment arms.^63^ Time and treatment arm will be included as fixed effect, while schools will be included as random effect to account for clustering. Mean cost and outcomes by treatment arm, as well as incremental cost and outcomes and incremental cost-effectiveness ratio (ICER), will be predicted from the chosen econometric model and reported alongside bootstrapped SEs. The uncertainty surrounding the estimate of incremental costs, QALYs and ICERs will be investigated by use of a non-parametric bootstrap of the cost and effect pairs for 1000 iterations. This uncertainty will then be presented on the cost-effectiveness plane with a 95% CI of the bootstrapped ICER estimated. Results will be summarised using a cost-effectiveness acceptability curve to reflect the probability of ESAS being cost-effective at various willingness-to-pay (WTP) thresholds. The £20 000–£30 000/QALY threshold that NICE typically considers cost-effective will be incorporated.

Within the CEA framework, there is no accepted threshold value for changes in the primary outcome. Therefore, sensitivity analysis using different WTP values will be performed. In addition to probabilistic sensitivity analysis, several scenarios will be explored in the deterministic sensitivity analysis.

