### Trial status

Schools are being recruited from September 2023 to December 2024 and baseline student surveys will be completed in October 2023 to December 2024. Schools are being randomised on completion of their baseline student survey.

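### The only survey source named for SAE prevalence is the baseline round, which precedes randomisation; the safety section should name the follow-up rounds

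*Protocol article*

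**What the plan says.** Under Child protection/safeguarding in the ESAS intervention and evaluation, the protocol article lists possible SAEs as incidents of sexual harassment and violence and the mental or physical ill health that follows from them. It then states: "We do not plan to specifically track SAEs in the trial because (a) these overlap with primary outcome data already collected by the trial". Its other two reasons are that such reports are sensitive and burdensome for schools to disclose, and that an SAE is unlikely ever to be attributable to the trial. As the quantitative alternative it says: "We will use the health resource use questions in the student baseline survey to track the likely prevalence of SAEs". It adds that check-in meetings with ESAS staff leads may supply further information, and that SAEs which become known go to the TSC chair within 24 hours. The process evaluation section keeps a monitoring log whose contents include adverse events.

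On timing, Recruitment and randomisation treats completion of the baseline survey as formal recruitment and continues: "At this point, schools will be randomised (1:1) using minimisation to ensure balance between arms in" three school characteristics. Trial status agrees: "Schools are being randomised on completion of their baseline student survey".

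On content, Secondary outcomes defines the service-use questions as the "number of appointments of each service type in the last 3 months". The first section on Study 3 says: "The data for the economic evaluation will be collected via the student baseline and follow-up surveys". The later one, having named the baseline and all follow-up surveys, says: "They will also include a bespoke resource use questionnaire designed to measure cross-sectoral health and social care use".

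**The concern.** To track prevalence in a trial is to follow it after allocation, in both arms, with a denominator. The survey round named for this purpose closes before a school knows its arm. Followed literally, the sentence yields a description of service use before treatment, which says nothing about the safety of ESAS.

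This matters because the protocol takes harm seriously elsewhere. It plans to study harmful as well as beneficial mechanisms, and it expects ESAS to increase disclosures. A rise in disclosure makes passively collected event reports hard to interpret, which is why a source collected in the same way in both arms is needed. The participants are school pupils, and participant safety is within the TSC's remit.

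**Working it through.** There is no stated figure to reproduce and no arithmetic on which the point depends. The check is a timeline, followed by a comparison of sections.

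**Step 1: order of events for one school.**

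| Order | Event | Section |
|---|---|---|
| 1 | Recall window opens, 3 months before the survey | Secondary outcomes |
| 2 | Baseline survey completed | Recruitment and randomisation; Trial status |
| 3 | School randomised | Recruitment and randomisation; Trial status |
| 4 | ESAS starts at once, or after 12 months | Study design |
| 5 | Follow-up surveys at 12 and 24 months | Measures |

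The round named for SAE prevalence covers steps 1 and 2 only. Its window closes before step 3, so it contains no time after randomisation in either arm.

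**Step 2: do later data of the same kind exist?** Yes. The service-use questions are listed as a secondary outcome, under a Measures heading that reads "Outcome measures (baseline, 12 months and 24 months" and covers all outcomes. Both Study 3 sections place resource-use data in the follow-up surveys. The safeguarding section is the only place that ties the questions to baseline alone.

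**Step 3: do the other safety routes give a rate by arm?**

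- Check-in meetings are described as something that may yield information. No schedule, denominator or uniform question is stated.
- The 24-hour rule applies only to events that happen to reach the study team.
- The monitoring log records what comes to attention.

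All three operate after randomisation, but none is systematic. Ascertainment may also differ by arm. Process measures are to be more detailed in immediate start schools, and all six case study schools, with their group discussions, observations and workshops, are immediate start. Counts of known events could be higher in that arm through contact alone.

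**Step 4: does overlap with the primary outcome cover the gap?** Only in part. The primary outcome is measured at 12 and 24 months in both arms. However, it is a binary indicator of any of five experiences, including name-calling, with an expected prevalence of 35%. It carries no severity, leaves forced sexual activity to a separate secondary item, and does not measure ill health.

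**Step 5: what would the 12-month round show?** With a 3-month recall, service use at 12 months covers roughly months 9 to 12 (12 − 3 = 9). That is a window late in the first year and not the whole year, but it is the same window in both arms, and the arms are then still on different conditions. At 24 months both arms have started ESAS, so that round no longer contrasts ESAS with no ESAS. Because the surveyed pupils change between baseline and 12 months, baseline can serve as a reference at school level, not pupil level.

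**The case against.** The strongest reply is that the sentence is probably a slip for the baseline and follow-up surveys. The questions are in every round, so no data are lost. Analyses of Study 1 already compares the secondary outcomes, including service use, forced sexual activity and mental well-being, by randomised allocation at 12 months with baseline adjustment. The first reason for not tracking SAEs relies on primary outcome data that are also collected after randomisation.

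Most of this stands, and it limits the point. A reader might infer that the trial has no safety information after the intervention starts, or that it could not detect an excess of harm. The documents support neither reading. The meetings, the 24-hour rule and the log all run after randomisation, and a harmful effect on the listed outcomes could emerge from the planned 12-month comparisons. Nor do the documents say that the committees would be given a baseline figure presented as SAE monitoring.

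What does not stand is that nothing needs changing. The article does not say that the wording is a slip, and the planned comparisons by arm are not linked to safety. As written, the one survey measure assigned to SAE prevalence cannot serve its purpose.

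**Conclusion.** The point holds in limited form. The safeguarding section names a pre-randomisation survey round as its only survey source for SAE prevalence, while other sections put the same questions in later rounds. The routes that remain are unsystematic, give no comparable rate by arm, and may capture more in immediate start schools.

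Its size is one misdirected sentence. The primary analysis, its power and the data collected are unaffected. The conclusion rests on reading the sentence literally, on the 3-month recall applying to the questions meant, and on randomisation following the baseline survey as two sections state. Unequal ascertainment is a reasonable expectation from the planned contact pattern; the documents do not establish it as fact.

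**What to change.** Reconcile the safeguarding section with the Study 3 sections by replacing the reference to the student baseline survey with the student baseline and follow-up surveys.

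Add that the safety summary reports, by allocated arm at 12 months, the service-use items, the forced-sexual-activity item and the well-being score. Clustering by school should be allowed for, and the school-level baseline used as reference. State the recall window beside each item, and treat the 24-month figures as descriptive.

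Send the summary to the TSC, which monitors participant safety, and to the data monitoring and ethics committee if wished. Keep the existing reporting of known SAEs alongside it, with a note that those counts may reflect differing contact with schools.

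The cost is one sentence of protocol wording and one table. No new questions, data collection or sample are needed.

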## Discussion

The ESAS evaluation will provide long overdue and urgently needed effectiveness, cost-effectiveness and implementation evidence on a UK intervention using a whole-school approach to address GBV, directly before it is implemented at scale. The study will also contribute empirical evidence on the scale and nature of sexual harassment in school via publication of baseline findings. This includes understanding of intersecting inequalities in experience of GBV at school, and how victimisation/perpetration of sexual harassment links with harmful gender norms,^67^ and school-level factors.

To our knowledge, this will be the first UK school-based trial to investigate the impact of whole-school approaches on school sexual harassment and GBV. Our type 1 implementation-effectiveness study design is novel in school-based evaluations. By using evaluation data to interrogate the programme theory, the trial will advance theory on mechanisms of sustainable change in whole-school approaches to tackling GBV. This will inform future decision-making regarding the transferability of ESAS to other contexts and wider roll-out.

The embedded economic evaluation within this study will identify and measure the resources needed to deliver such a GBV prevention intervention along with any short-term health and social care resource use. This study will also assess intervention impacts on school pupil’s health-related quality of life which will be combined with costs to generate cost-effectiveness evidence.

The study will enhance understanding of how systemic factors in schools can deter or facilitate interventions to address GBV in schools. We will build on learning from participatory systems mapping of factors shaping school prevention and response to sexual harassment during the pretrial pilot phase.^33^ Finally, the trial will seek to advance methods of systems-informed evaluation of complex interventions. The process evaluation and study of longitudinal outcomes are designed to explore if and how ESAS combines with the context; alters relationships between actors; facilitates cultural change; leads to shifts in the distribution of resources; and replaces other activities during and beyond the intervention period.^52^

